# GA101 (obinutuzumab) monocLonal Antibody as Consolidation Therapy In CLL (GALACTIC) trial: study protocol for a phase II/III randomised controlled trial

**DOI:** 10.1186/s13063-017-2107-0

**Published:** 2017-07-26

**Keywords:** Chronic lymphocytic leukaemia (CLL), Obinutuzumab, GA-101, Consolidation, Phase II/III trial, Minimal residual disease (MRD), Randomised controlled trial (RCT)

## Abstract

**Background:**

Chronic lymphocytic leukaemia (CLL) is the most common adult leukaemia. Achieving minimal residual disease (MRD) negativity in CLL is an independent predictor of survival even with a variety of different treatment approaches and regardless of the line of therapy.

**Methods/design:**

GA101 (obinutuzumab) monocLonal Antibody as Consolidation Therapy In CLL (GALACTIC) is a seamless phase II/III, multi-centre, randomised, controlled, open, parallel-group trial for patients with CLL who have recently responded to chemotherapy. Participants will be randomised to receive either obinutuzumab (GA-101) consolidation or no treatment (as is standard). The phase II trial will assess safety and short-term efficacy in order to advise on continuation to a phase III trial. The primary objective for phase III is to assess the effect of consolidation therapy on progression-free survival (PFS). One hundred eighty-eight participants are planned to be recruited from forty research centres in the United Kingdom.

**Discussion:**

There is evidence that achieving MRD eradication with alemtuzumab consolidation is associated with improvements in survival and time to progression. This trial will assess whether obinutuzumab is safe in a consolidation setting and effective at eradicating MRD and improving PFS.

**Trial registration:**

ISRCTN, 64035629. Registered on 12 January 2015.

EudraCT, 2014-000880-42. Registered on 12 November 2014.

**Electronic supplementary material:**

The online version of this article (doi:10.1186/s13063-017-2107-0) contains supplementary material, which is available to authorized users.

## Background

Chronic lymphocytic leukaemia (CLL) is the most common adult leukaemia. The CLL8 trial [1, 2] has shown that even though almost double the number of patients receiving fludarabine, cyclophosphamide and rituximab (FCR) achieved minimal residual disease (MRD) negativity (defined as <0.01% CLL cells) compared with those receiving fludarabine and cyclophosphamide, once low-level MRD was achieved, both arms showed the same prognostic significance. This indirectly implies that the depth of the remission may be more important than the type of treatment given to attain that remission. Attainment of MRD negativity has also been demonstrated as an independent predictor of overall survival (OS) and progression-free survival (PFS) even with a variety of different treatment approaches and regardless of the line of therapy [3].

The researchers in the U.K. National Cancer Research Institute (NCRI) CLL207 phase II trial [4] assessed whether participants with low levels of disease could attain MRD negativity following consolidation therapy with alemtuzumab. The results showed good efficacy, with 39 (83%) of 47 participants who were consolidated attaining MRD negativity. Overall, 38% remained MRD-negative in the peripheral blood 6 months after therapy, which may be the true MRD-negative population because this represents the time for redistribution of the disease among various compartments following antibody treatment. After a median follow-up of 44 months, the participants who were MRD-negative 6 months after treatment had a significantly increased PFS time compared with those participants who were MRD-positive, with a median PFS at 3 years of 94.4% in MRD-negative participants compared with 60.0% in MRD-positive participants (*p* = 0.004). However, alemtuzumab had a significant toxicity profile, with 22 serious adverse event (SAEs), 4 of which were clinically unacceptable (1 pneumocystis pneumonia, 1 parainfluenza-related death and 2 Epstein-Barr virus-related transformed diseases), reported in 17 (36.2%) participants.

Obinutuzumab (GA-101) is a novel monoclonal antibody and has been shown to have greater efficacy in CLL than previous anti-CD20 antibodies [5, 6], with reports of MRD negativity when used to treat progressive CLL. In addition, because the cells targeted by obinutuzumab are B cells rather than all lymphocytes (including T cells), obinutuzumab is likely to be significantly less immunosuppressive than alemtuzumab. The study of obinutuzumab within the clinical trial setting has demonstrated a rapid response in peripheral blood lymphocytosis, with early reports of patients achieving MRD negativity with obinutuzumab [7–9].

### Rationale for therapeutic study

MRD-negative patients have a survival advantage in comparison to MRD-positive patients, regardless of the approach used to achieve MRD negativity. This is a seamless phase II/III randomised trial in which we will test whether consolidation with obinutuzumab to eradicate MRD leads to prolonged PFS.

## Methods/design

### Trial design

This is a seamless phase II/III, multi-centre, randomised, controlled, open, parallel-group trial for patients with CLL who have recently responded to chemotherapy. Patients with detectable MRD (MRD-positive) will be randomised to receive either consolidation therapy with obinutuzumab or no consolidation therapy (as is currently standard) (Fig. 1). The consolidation treatment period is approximately 3 months. Participants who are MRD-negative at baseline will be followed but not randomised. A schedule of enrolment, interventions and assessments is provided in Figs. 2 and 3, and a populated Standard Protocol Items: Recommendations for Interventional Trials (SPIRIT) checklist for this article is also provided (Additional file 1).

**Fig. 1 Fig1:**
[figure not shown]
Trial flow diagram. *BM* Bone marrow, *CLL* Chronic lymphocytic leukaemia, *CTRU* Leeds Clinical Trials Research Unit, *HMDS* Haematological Malignancy Diagnostic Service, *MRD* Minimal residual disease, QoL Quality of life

**Fig. 2 Fig2:**
[figure not shown]
Schedule of enrolment, interventions and assessments for participants who are suitable for randomisation. *MRD* Minimal residual disease, *PFS* Progression-free survival. ^1^To be performed after the analysis of peripheral blood and only in participants whose peripheral blood is MRD positive. ^2^ To be performed within 4 weeks of randomisation and before treatment is started. ^3^Only for participants randomised to obinutuzumab and if appropriate clinically. ^4^Only required for participants randomised to treatment with obinutuzumab. ^5^Serum immunoglobulins and electrophoresis only. ^6^Tested Centrally

**Fig. 3 Fig3:**
[figure not shown]
Schedule of enrolment, interventions and assessments for participants who are MRD-negative by blood analysis. *CT* Computed tomography, *MRD* Minimal residual disease, WHO World Health Organisation. ^1^If appropriate clinically. ^2^Tested Centrally

### Trial objectives

The trial has a seamless phase II/III design with separate primary objectives for each phase (Fig. 4). The primary objectives in phase II are to determine the rate of achieving MRD negativity at two pre-defined stages and assess the safety of obinutuzumab in a consolidation setting. The primary objective in phase III is to compare consolidation therapy with obinutuzumab against no consolidation therapy with respect to PFS in participants who responded to previous therapy with a complete remission (CR) or good partial remission (PR) with low levels of MRD.

**Fig. 4 Fig4:**
[figure not shown]
Statistical design. *CT* Computed tomography, *MRD* Minimal residual disease, WHO World Health Organisation

The following are secondary objectives:To assess the eradication of detectable MRD, OS and time to next treatment following consolidation therapy with obinutuzumabTo compare OS following consolidation therapy with obinutuzumab against no consolidation therapyTo compare time to next treatment for obinutuzumab consolidation against no consolidationTo evaluate response rate, defined as CR or PR by International Workshop on Chronic Lymphocytic Leukemia criteria [10], following consolidation therapy with obinutuzumabTo evaluate and compare PFS and OS in participants who are and who become MRD-negativeTo assess the safety and toxicity of obinutuzumabTo assess quality of life (QoL)

### Trial population

Patients who are eligible for the trial must be at least 18 years old, have previous confirmation of CLL, have undergone between one and three regimens of chemotherapy previously ending between 3 and 24 months before enrolment, have a peripheral B-cell count of <5 × 10^9^/L, have a response to the most recent chemotherapy treatment for CLL with PR, complete remission with incomplete marrow recovery (CRi) or CR. The patient must also be capable of giving written consent and have a World Health Organisation (WHO) performance status of 0 or 1.

Patients with any of the following characteristics are excluded from the trial: disease progression after response to last therapy, active infection, previous anaphylaxis to monoclonal antibodies, previous treatment with obinutuzumab, central nervous system involvement in CLL, mantle cell lymphoma, other severe concurrent diseases or mental disorders that could interfere with their ability to participate in the study (including moderate or worse cardiac diseases), known HIV positivity, positive serology for hepatitis B or C virus, persisting severe pancytopenia (neutrophils <0.5 × 10^9^/L or platelets <50 × 10^9^/L) or transfusion-dependent anaemia, vaccination with a live virus within 28 days, active haemolysis (patients with haemolysis controlled with prednisolone at a dose 10 mg or less per day can be entered into the trial), creatinine and bilirubin less than two times the upper limit of normal, previously treated with an allogeneic stem cell transplant, pregnant or lactating women, or women/men who are capable of conceiving children and who are unwilling to use appropriate medically approved contraception during and for 18 months after receiving treatment.

Once participants provide consent for the trial, peripheral blood will be tested for MRD. Patients who are MRD-negative will not be eligible for randomisation but will still be followed annually for MRD. Patients who are MRD-positive will have bone marrow and trephine samples tested centrally to confirm MRD level in the aspirate, a stratification factor for randomisation. To be randomised, participants must have an MRD-positive peripheral blood sample between 3 and 24 months since completing the last treatment for CLL and be confirmed as MRD-positive in the bone marrow. Participants must also have clinically and radiologically confirmed absence of lymphadenopathy (largest lymph node 1.5 cm or less in minimum diameter).

### Sample size

The overall sample size of the trial is powered for the phase III primary endpoint of PFS. An internal literature review investigating patients who have received up to three lines of previous therapy of any type and who responded to their most recent therapy with at least a PR suggested that 3 years is a reasonable estimate for median PFS in the control population (i.e., no consolidation), which translates to approximately 2 years from the time the participants are randomised (because it will be 3–24 months after previous therapy). An important clinical improvement would be an increase in median PFS from 2 to 3.3 years, a relatively large improvement, because consolidation is given at a time when patients would otherwise be in remission and treatment-free. The trial is powered to test the null hypothesis of no difference in PFS between the treatment arms, with a two-sided 5% level of significance and 80% power. Assuming 3 years of recruitment, 3 years of follow-up and allowing for a 5% drop-out rate, 188 participants are required (94 per arm) in order to observe 120 progression/death events. Losses to follow-up for the primary endpoint are expected to be extremely uncommon due to the short treatment duration and straightforward and regular follow-up schedule. A formal interim analysis on PFS will be carried out and reported to the data monitoring and ethics committee (DMEC) when half the required number of events have been observed (60 events).

The O’Brien and Fleming alpha-spending function [11] will be used to adjust for multiple testing to conserve the overall type I error, which recommends that the interim results be compared with a *p* value of 0.005, and the final analysis results are then compared with a *p* value of 0.047.

Because obinutuzumab has not previously been used in a consolidation setting, the short-term endpoint of MRD negativity will be assessed to determine whether continuation to the phase III part of the trial is worthwhile. Because it may take up to 9 months from recruiting the last participant to the time of analysis to determine their MRD response, there will be a two-stage phase II design to allow the first stage to be reviewed as early as possible and prior to the completion of recruitment to the second stage (Fig. 4). It is not planned to pause recruitment to wait for the phase II outcomes, but the DMEC, on review of the safety and early efficacy data, can choose to implement this should they feel it necessary.

Simon’s two-stage optimal design [12] will be used to set stopping bounds at each stage of the analysis (Fig. 4). A negativity rate above 35% would deem the therapy active, and a success rate below 15% would deem the therapy inactive. Participants randomised to consolidation therapy with obinutuzumab who receive at least 4 weeks of treatment will be included in the phase II populations. With a 10% significance level and 80% power, the trial will continue after the first stage if, among the first nine participants, at least two (22%) achieve MRD negativity. The trial will continue after the second stage into the phase III part of the trial if, among the first 23 participants, at least 6 (26%) achieve MRD negativity. Patients recruited during phase II will contribute to the final phase III target of 188 patients.

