### Primary endpoint analyses

The phase II primary endpoint of MRD negativity in each stage of the phase II part of the trial will be assessed once 9 and 23 participants have received at least 4 weeks of obinutuzumab treatment and been followed until 6 months post-randomisation. The phase III primary endpoint of PFS will be assessed once 120 events (progressions/deaths) have been observed overall. A formal interim analysis will be carried out when 60 events have been observed overall in order to allow large differences between the trial arms to be reported early (Fig. 4). PFS is defined as the time from randomisation to first documented evidence of progression or death. Participants not having progressed or died or who are lost to follow-up at the time of the phase III analyses will be censored at the last date they were known to be alive and progression-free. For the analysis of primacy, we will use a Cox proportional hazards model [15] to compare the trial arms, adjusting for the minimisation factors, to calculate the HR and corresponding 95% CIs. The *p* value to assess for statistical significance will be compared with 0.047 to account for the formal interim analysis. In addition, median survival estimates with corresponding 95% CIs, as well as Kaplan-Meier curves [16], will be produced by trial arm.

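### The 3–24 months elapsed since therapy do not turn a 3-year median PFS into 2 years from randomisation, so the projection of 120 events in 3+3 years lacks a stated basis

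*Protocol article*

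**What the plan says.** The Sample size section of the protocol article reports an internal literature review of patients who responded to their latest therapy and takes 3 years as the control median PFS. It does not say from which date those 3 years run. It continues: "which translates to approximately 2 years from the time the participants are randomised". The only reason offered is "because it will be 3–24 months after previous therapy".

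The target is "an increase in median PFS from 2 to 3.3 years", with a two-sided 5% level and 80% power. With 3 years of recruitment, 3 years of follow-up and 5% drop-out, the section concludes that "188 participants are required (94 per arm) in order to observe 120 progression/death events".

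Three other statements bear on the conversion:

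- Trial population lists among the exclusions "disease progression after response to last therapy".
- The same section requires an "MRD-positive peripheral blood sample between 3 and 24 months since completing the last treatment for CLL", with confirmation in the marrow.
- Primary endpoint analyses states: "PFS is defined as the time from randomisation to first documented evidence of progression or death". The final PFS analysis is triggered by 120 events.

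**The concern.** The step from 3 to 2 years looks like a subtraction of elapsed time. The midpoint of 3–24 months is 13.5 months, or 1.125 years, and 3 − 1.125 = 1.875, about 2. Subtraction would be right only if nobody could progress between the end of therapy and randomisation. In fact some responders do progress in that interval and are excluded. Those who are randomised have already come through it, so their median from randomisation is longer than the subtraction suggests.

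The control median sets the event rate, and the event rate links 188 participants and 3+3 years to 120 events. If the median is too short, the events arrive later than the protocol says.

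**Working it through.** **Inputs.** From Sample size: source median 3 years; design medians 2 and 3.3 years; two-sided 5%, 80% power; accrual A = 3 years, minimum follow-up F = 3 years; 5% drop-out; N = 188 (1:1); 120 events. From Trial population: entry at 3–24 months, progression-free. Assumed here, because the document does not state them: uniform accrual; exponential PFS for the first reproduction; later, Weibull shapes and uniform entry over 0.25–2 years.

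**1. Reproducing the plan's figures.** Events by Schoenfeld: D = 4(1.960 + 0.842)² / (ln HR)².

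- HR 0.60 (3.3 read as a rounded 3.33): D = 120.3, and power at 120 events is 79.9%.
- HR 2/3.3 = 0.606: D = 125.2, and power at 120 events is 78.3%.

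Probability of an event, with λ = ln 2 / median: P = 1 − [exp(−3λ) − exp(−6λ)] / (3λ).

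- Median 2: P = 0.780. Median 3.3: P = 0.605. Mean 0.693.
- Expected events: 188 × 0.95 × 0.693 = 123.7.
- N for 120 events: 120 / 0.693 / 0.95, about 183.

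So constant hazard with a 2-year control median approximately reproduces 188 and 120.

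**2. The conversion from 3 to 2 years.** For a patient progression-free at time t, the residual median m solves S(t + m) = S(t)/2. With a 3-year median, S(3) = 0.5, so the chance of still being progression-free at 3 years is 0.5/S(t). This exceeds 0.5 whenever S(t) < 1. Hence m > 3 − t for every survival curve, and the subtraction is only a lower bound. Under constant hazard, m = 3 years for every t.

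**3. Projection with a 3-year residual median, constant hazard, design HR kept.**

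- HR 0.60 (3 vs 5 years): P = 0.639 and 0.460, mean 0.550; 188 × 0.95 × 0.550 = 98.2 events.
- HR 0.606 (3 vs 4.95 years): 98.5 events.
- Shortfall against 120: about 18%.
- Solving 188 × 0.95 × mean P(F) = 120 for F gives 4.8 years after last entry, instead of 3.
- Power if the analysis were done at 6 years regardless: 71.6% (HR 0.60) or 70.0% (HR 0.606).

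**4. Range by hazard shape.** Weibull with a 3-year median from end of therapy, S(x) = exp[−ln 2 · (x/3)^k]. The residual median at t is (3^k + t^k)^(1/k) − t. Entry times are weighted by being progression-free at entry; HR 0.60; 5% drop-out.

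| Shape k | Residual median at t = 1.125 y | Events at 3+3 years |
|---|---|---|
| 0.9 | 3.28 | 92 |
| 1.0 | 3.00 | 98 |
| 1.25 | 2.56 | 112 |
| 1.5 | 2.32 | 124 |
| 2.0 | 2.08 | 143 |

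The projection reaches 120 by year 6 at a shape of about 1.4.

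**The case against.** **No distribution is named.** An exponential formula applied from randomisation roughly returns 188, but that does not commit the trial to constant hazard from end of therapy. With a rising hazard the residual median falls, and at shape 2 it is 2.08 years, which could fairly be called about 2. This stands: a reader might infer that the design will give 98 events instead of 120, but 98 is one conditional figure in a range lying on both sides of 120.

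**The origin of the 3 years is not given.** If it ran from the start of a course lasting about 6 months (an assumption), the mid-window elapsed time would be 1.625 years. Subtraction would give 1.375 years, and the residual median at shape 1.5 would be 2.1. This also stands as an uncertainty.

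**Only MRD-positive patients are randomised, and the Background says they do worse.** As an illustration with assumed values, suppose 30–40% of the reviewed responders were MRD-negative with a PFS hazard ratio of 0.3–0.4. A pooled 3-year median then implies about 2.0–2.35 years in the MRD-positive group even under constant hazard. So a reader should not infer that 3.0 years is the correct design value. However, the section does not give MRD status as its reason. The one MRD-positive figure in the Background, 60% progression-free at 3 years after alemtuzumab, does not yield a 2-year median.

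**Power is protected by the event trigger.** At a fixed HR, power depends on the number of events, not on the control median. This stands. It is tempting to say that the trial is underpowered at 70–72%, but that needs an analysis at 6 years on about 98 events, which the document does not provide for. Keeping the absolute gain (3 to 4.3 years, HR 0.70) would give about 50% power at 120 events, but that is a different target from the one stated.

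**Conclusion.** The point holds as a defect in the stated derivation. Elapsed time alone cannot reduce a 3-year median to 2 years when patients who have progressed are excluded, and this is true for any survival curve. The document gives no other ground for the 2 years.

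The size is conditional. If the 3 years runs from end of therapy and the hazard is constant, 188 participants give about 98 events at 3+3 years, and 120 come about 4.8 years after last entry. Over Weibull shapes 0.9 to 2 the range is about 92 to 143 events, and 120 is reached by year 6 only with a rising hazard of shape about 1.4 or more. Selection of MRD-positive patients could also shorten the control median, by an amount the document does not quantify.

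The main consequence is a possibly much longer time to the final analysis. The type I error is unaffected, and power at 120 events is unaffected for a given HR.

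**What to change.** Keep 188 participants and 120 events, and change the Sample size text as follows:

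1. Replace the subtraction with a conditional residual median under a named hazard model, stating the time origin of the 3-year figure. Alternatively, give a separate estimate for MRD-positive patients as the basis for 2 years.
2. Restate the expected events at 3+3 years and the expected time to 120 events, with a range over plausible hazard shapes (about 98 events and 4.8 years after last entry under constant hazard; about 92 to 143 events over shapes 0.9 to 2).
3. State the target effect as a hazard ratio. HR 0.60 gives 80% power at 120 events. If 2 versus 3.3 years (HR 0.606) is kept, state the power as about 78%. Rounding to HR 0.61 would give 77%, so it should not be paired with 80%.

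The cost is a re-run of the event projection and a few sentences. No participants are added, and the significance level, event target and analysis method stay as they are. The stated time to analysis may become less favourable. Trial status reports recruitment closed in February 2017, so the practical use of the correction is in forecasting and explaining when the PFS analysis can take place.
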